**Methods/Design:**

The study is three-armed: a prospective cluster-randomized comparison of two interventions (DMP 1 and DMP 2) against routine care without DMP as control group. In the DMP group 1 the patients are treated according to the current situation within the German-Diabetes-DMP. The DMP group 2 represents diabetic care within ideally implemented DMP providing additional interventions (e.g. quality circles, outreach visits). According to a sample size calculation a sample size of 200 GPs (each GP including 20 patients) will be required for the comparison of DMP 1 and DMP 2 considering possible drop-outs. For the comparison with routine care 4000 patients identified by diabetic tracer medication and age (> 50 years) will be analyzed.

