#### Selection of participants

500 GPs in Rheinland-Pfalz and 500 GPs in Sachsen-Anhalt participating in the Diabetes-DMP will be recruited by an invitation letter giving information about the study project. From those who will accept to participate, 100 GPs will be randomized in the DMP group 1 and 100 in the DMP group 2. All patients with a type 2 diabetes out of these practices insured at the general regional health funds (*Allgemeine Ortskrankenkassen = AOK*) and participating in the DMP will be included in the study then. Incomplete participation in the interventions will be an exclusion criterion in the DMP group 2.

For the control group 4000 AOK patients out of practices not participating in the DMP will be detected through diabetes tracer medication and age (> 50 years) and will be matched. Participation in a DMP offered by another health fund is an exclusion criterion in the control group.

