### Data collection and analysis

All data will be provided by the AOK. Data of the DMP groups are retrieved by the DMP documentation forms which have to be completed routinely every 3 to 6 months during the scheduled DMP visits of participating patients. The information about the tracer medication identifying patients of the control group is also provided by the AOK. The data reporting will follow the CONSORT recommendations for cluster randomized trials [16].

Data analysis will be performed according to the intention-to-treat (ITT) method. For missing data the 'last observation carried forward' -method will be used.

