#### Outcome-parameter

Outcome parameters were defined considering best available evidence, legal regulations and feasibility. According to our two scientific hypotheses two groups of outcome parameters were defined: "outcome parameters I" for the comparison of the DMP groups and "outcome parameters II" for the comparison of DMP and routine care. This differentiation of the outcome parameters is essential because in the control group availability of patient data will be limited to process indicators only. The outcome parameters are displayed in Table 1.

**Table 1 T1:** Primary and secondary outcome parameters

**OUTCOME PARAMETERS I**	**OUTCOME PARAMETERS II**
**DMP 1 vs. DMP 2**	**DMP 1 vs. CG**
***Primary outcome parameter***	***Primary outcome parameter***

Proportion of patients achieving target values for HbA1c and RR according to the legal regulations (10)	Proportion of patients with prescriptions for antidiabetic, antihypertensive and lipid-lowering drugs

***Secondary outcome parameters***	***Secondary outcome parameters***

Proportion of patients with prescriptions for antidiabetic, antihypertensive and lipid-lowering drugs	----
Proportion of patients with referrals to ophthalmologists, specialists for diabetology and diabetic feet	Proportion of patients with referrals to ophthalmologists, specialists for diabetology and diabetic feet
Proportion of patients referred to a patient education training for diabetes and hypertension	Proportion of patients referred to a patient education training for diabetes and hypertension
Proportion of patients with severe complications (amputation, dialysis etc.)	Proportion of patients with severe complications (amputation, dialysis etc.)
Proportion of patients with > 2 hospitalizations in the last 6 months	Proportion of patients with > 2 hospitalizations in the last 6 months
Consultation rate	Consultation rate
Days of incapacity to work	Days of incapacity to work
Mean differences of HbA1c, RR, BMI and glomerular filtration rate	---
SCORE risk chart (RR, cholesterol, smoking status, age, gender)	---
Drop out rate from the DMP	---

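### DMP 1 and control patients are picked by different rules: controls must be drug-treated and over 50, DMP 1 patients need not be, and type 2 diabetes is required only in the DMP arms

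*Protocol article*

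**What the plan says.** Selection of participants in the Protocol article sets two separate entry rules.

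- **DMP arms:** "All patients with a type 2 diabetes out of these practices insured at the general regional health funds" and enrolled in the DMP are included. No lower age limit and no requirement of drug treatment is stated.
- **Controls:** the source is given as "For the control group 4000 AOK patients out of practices not participating in the DMP", and these patients "will be detected through diabetes tracer medication and age (> 50 years) and will be matched". The Abstract repeats the rule: "4000 patients identified by diabetic tracer medication and age (> 50 years) will be analyzed". The exclusion stated for controls is: "Participation in a DMP offered by another health fund is an exclusion criterion in the control group".

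Data collection and analysis adds only the source of the signal: "The information about the tracer medication identifying patients of the control group is also provided by the AOK". The drug classes that count as tracer and the variables used for matching are not named.

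Table 1 (Outcome-parameter) gives the primary outcome for DMP 1 versus control: "Proportion of patients with prescriptions for antidiabetic, antihypertensive and lipid-lowering drugs". The same section says that "in the control group availability of patient data will be limited to process indicators only". The Discussion describes this part of the study as quasi-experimental, with non-random allocation to control.

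**The concern.** Hypothesis 1 asks whether the type 2 diabetes programme does better than routine care. That contrast is readable only if both groups could have qualified under the same conditions apart from the programme. Here they could not, in three respects.

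- **Drug treatment.** A control is found because of a diabetes drug, and antidiabetic prescription is part of the primary outcome. At identification that component is 100% in controls by construction. DMP 1 may contain patients without drug treatment.
- **Age.** Only controls must be over 50. Prescribing of antihypertensive and lipid-lowering drugs, the other parts of the primary outcome, can be expected to vary with age.
- **Diabetes type.** DMP 1 is restricted to type 2. A drug signal plus an age limit does not confirm type 2. If insulin counts as a tracer drug, some controls may have type 1 diabetes.

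Allocation is not random, so nothing balances these differences by chance. The 4000 controls reduce random error but not a difference built into the entry rules.

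**Working it through.** **Step 1. The rules side by side**

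| Condition | DMP 1 | Control |
|---|---|---|
| Type 2 diabetes | required | not stated |
| Diabetes drug | not required | required (tracer) |
| Age over 50 | not required | required |
| DMP | enrolled | non-DMP practices; other funds' DMP excluded |

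Only the last row is the exposure under study. The first three are differences in who can enter.

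**Step 2. The plan's own figures**

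Sample size calculation and Selection of participants give 200 GPs, 20 patients each, 100 GPs per DMP arm, ICC 0.05, and 4000 controls.

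- DMP patients: 200 × 20 = 4000, or 2000 per arm.
- Design effect: 1 + (20 − 1) × 0.05 = 1.95.
- Effective size per DMP arm: 2000 / 1.95 ≈ 1026.

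The 200 GPs cannot be re-derived, because the article gives no error rates or event rates. The point does not depend on that figure.

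For scale, assume two-sided alpha 0.05, 80% power and a 50% base rate, where the variance is largest. DMP 1 versus control can then detect about 4.9 points if controls are treated as unclustered, or about 5.4 points with the same design effect in controls (4000 / 1.95 ≈ 2051).

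**Step 3. Selection on the antidiabetic component**

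Let u be the share of DMP 1 patients without an antidiabetic drug. The document gives no value, so u is assumed. At identification:

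gap = 100% − (100% − u) = u

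For u = 10%, 20% or 30% the gap is 10, 20 or 30 points. That is about 2 to 6 times the detectable difference (10 / 5.4 ≈ 1.9; 30 / 4.9 ≈ 6.1). Whatever u is, DMP 1 cannot exceed controls on this component at identification.

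**Step 4. Possible type 1 admixture**

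Shift in the control proportion = s × (p1 − p2), where s is the type 1 share among controls and p1, p2 are the outcome proportions in type 1 and type 2. All three are assumptions: s = 2%, 5%, 10%, and antihypertensive prescription p1 = 40%, p2 = 65%.

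- s = 2%: 0.02 × (−25) = −0.5 points
- s = 5%: 0.05 × (−25) = −1.25 points
- s = 10%: 0.10 × (−25) = −2.5 points

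Standard error of the difference, with p = 0.65 and p(1 − p) = 0.2275:

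- Controls unclustered: √(0.2275 × 1.95 / 2000 + 0.2275 / 4000) = 1.67 points
- Controls with design effect 1.95: √(0.2275 × 1.95 / 2000 + 0.2275 × 1.95 / 4000) = 1.82 points

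The shift is therefore 0.5 / 1.82 ≈ 0.3 to 2.5 / 1.67 ≈ 1.5 standard errors.

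On the antidiabetic component, type 1 admixture adds nothing at identification: every control holds such a prescription, so the shift is s × (100% − 100%) = 0.

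Specialist referral, a secondary outcome, moves more under assumed rates of 60% versus 15%: 0.9 to 4.5 points, against standard errors of 1.25 to 1.37. The top of that range needs the highest assumed share.

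**Step 5. Age**

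The article gives neither the share of DMP 1 patients aged 50 or under nor their prescribing rates. No size can be derived.

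**The case against.** A reader might infer that type 1 patients do enter the control arm and do bias the result. The article does not support this. It never lists the tracer drugs, and a tracer limited to oral agents would largely miss type 1 diabetes. The age limit lowers the type 1 share and may have been meant as a proxy for type 2. It would also go too far to say that prescription data or the unnamed matching variables can reveal nothing about type: drug class carries partial information, and the fix below relies on it. The tracer list and matching variables are details that a condensed article may leave to the full protocol, so their absence is not a defect in itself. These objections stand, and they reduce the type 1 part to a possibility of unknown size and direction.

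They do not remove the other two asymmetries, which need no assumption about the tracer list. Matching cannot supply an untreated control, or one aged 50 or under, because the control rule admits none. It could help only if the DMP 1 patients concerned were dropped, which the article does not state.

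The Discussion calls this part a controlled before-after study, and a constant level difference would partly cancel in a comparison of changes. The same section says that baseline values of DMP patients were not documented, so cancellation is not assured. Nor would it cure the selection on drug treatment: controls start at 100% on the antidiabetic component and can only stay or fall, while untreated DMP 1 patients can only stay or rise. Calling the design quasi-experimental is candid, but it does not address unequal entry rules that could be aligned.

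**Conclusion.** The point holds in this form: the stated rules make the two arms of the DMP 1 versus control comparison differ by construction in drug treatment and age, and they leave diabetes type unconfirmed in controls. Selection on part of the primary outcome is the main defect. At identification it equals the share of DMP 1 patients without antidiabetic drugs, or 10 to 30 points if that share is 10 to 30%. The age difference is certain as a rule, but its effect cannot be sized.

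Type 1 admixture is secondary and conditional on the tracer including insulin. For the one primary-outcome component where it was sized, antihypertensives, it is about 0.5 to 2.5 points, or 0.3 to 1.5 standard errors, under wholly assumed shares and rates. The change should be made, with medium confidence in how much it matters. The randomised comparison of DMP 1 with DMP 2 is not affected.

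**What to change.** For the DMP 1 versus control analysis, apply one common rule to both arms from AOK prescription data: age over 50 and at least one oral antidiabetic prescription before inclusion. If AOK data carry a type-specific diagnosis, use instead age over 50, any tracer drug and exclusion of type 1, again in both arms; this keeps insulin-only type 2 patients. Keep the all-tracer control set as a sensitivity analysis. State the tracer drug list and the matching variables alongside the rule; if the tracer already excludes insulin, saying so largely settles the type 1 part.

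The work is one additional filter on data the AOK is already to supply, and some replacement controls may have to be drawn. DMP 1 patients aged 50 or under or without drug treatment leave this comparison, as do insulin-only type 2 patients under the oral-drug rule, so the conclusion covers a narrower population than Hypothesis 1 names. Both arms would also start at 100% on the antidiabetic component, which then says little about starting drug treatment.

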### Scientific hypotheses

• The German-Diabetes-DMP (DMP 1) is more effective than routine diabetes care (CG)

• An optimally implemented form of the Diabetes-DMP (DMP 2) is more effective than the German-Diabetes-DMP (DMP 1).

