## Discussion

There are specific difficulties in evaluating the effectiveness of complex interventions such as disease management programs [19], particularly, in our case that implementation process has already started [15]. At the moment it is not conceivable to which phase of the implementation process the DMP actually has preceded. However, the DMP group 2 represents an ideal implementation of the DMP within the scope of the German law regulation.

To adapt the evaluation design to the real conditions of diabetes care in Germany at the moment, but also to consider the ongoing implementation process we have chosen the design of a prospective randomized-controlled comparison of the two DMP groups embedded in the quasi-experimental design of a controlled before-after study with a blinded control group. The quasi-experimental design is predetermined because allocation to the control group can not be perfomed randomly and because baseline values for patients participating in the DMP have not been documented.

A fully experimental design with a randomized control group was rejected by the authors, because this could create an artificial care situation. That is informing patients and GPs of the control group about the study and probably asking for completing any questionnaires would introduce an enormous bias.

According to the theoretical model for design and evaluation of complex interventions by Campbell et al the presented study can be assigned to phase III and IV (15, 20). However, pilot projects have shown that an observation period of 24 months will be too short to show significant differences in severe clinical endpoints (i.e. amputations, diabetic renal insufficiency, cardio-vascular events). Therefore it was decided to have a combination of HbA1c and blood pressure as primary endpoint in the randomized part of the trail and prescriptions in the quasi-experimental part of the trial.

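### Controls are selected on a diabetes prescription and DMP 1 patients are not, yet that prescription is one of three components of the primary outcome for DMP 1 versus control, so the component cannot be interpreted as written

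*Protocol article*

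**What the plan says.** The entry rules are in the protocol article under Selection of participants. For the two DMP groups they take in "All patients with a type 2 diabetes out of these practices insured at the general regional health funds" who take part in the DMP; no drug or age condition is given. The other source is described as "For the control group 4000 AOK patients out of practices not participating in the DMP", and these patients "will be detected through diabetes tracer medication and age (> 50 years) and will be matched". The matching variables are not named.

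Table 1, under Outcome-parameter, gives one primary outcome for DMP 1 versus control: "Proportion of patients with prescriptions for antidiabetic, antihypertensive and lipid-lowering drugs". It does not say whether the three classes are analysed separately or jointly. This outcome carries the first hypothesis, that DMP 1 is more effective than routine care.

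The Discussion describes the randomised DMP comparison as "embedded in the quasi-experimental design of a controlled before-after study with a blinded control group". It explains the quasi-experimental choice partly by the fact that "baseline values for patients participating in the DMP have not been documented".

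**The concern.** At selection, a control without a diabetes drug cannot exist, whereas a DMP 1 patient without one can. The antidiabetic component is thus near its maximum in controls because of how they were found, not because of the care they received. In DMP 1 it reflects the real mix of drug-treated and untreated patients. The age limit, stated for controls only, adds a second difference between the groups, which the documents do not allow one to size.

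Allocation in this comparison is not random, so nothing in the design balances the two groups on drug treatment. A larger sample does not help; it only makes the artefact more clearly significant. At stake is the only primary test of the first hypothesis: its result could come from the selection rule rather than from any effect of the programme.

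**Working it through.** **The plan's own figure.** The article gives no calculation for DMP 1 versus control; it states only that there are 4000 controls. The 200 GPs are sized for DMP 1 versus DMP 2. That figure cannot be reproduced from the article, which gives no error rates, event rates or drop-out rate, and the point does not depend on it.

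**Inputs from the protocol article.**
- DMP 1: "100 GPs will be randomized in the DMP group 1 and 100 in the DMP group 2", with 20 patients per GP, gives 100 × 20 = 2000 patients.
- Controls: 4000 patients.
- ICC: 0.05 (Sample size calculation).

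**Inputs assumed.**
- Share of DMP 1 patients without an antidiabetic drug: 10, 20 or 30%.
- No true DMP effect, and no matching on medication.
- For the joint outcome: the other two classes are both present in 30% of each group, independently of antidiabetic use.
- For controls: the same design effect as for DMP 1.

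**Design effect.** 1 + (20 − 1) × 0.05 = 1.95.

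**Antidiabetic component at follow-up, controls at 100%.** SE of the DMP 1 proportion = √(p(1 − p) × 1.95 / 2000). Controls at exactly 100% add nothing to it.

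| Untreated in DMP 1 | DMP 1 | Controls | Difference (points) | SE (points) | Difference / SE |
|---|---|---|---|---|---|
| 10% | 90% | 100% | −10 | 0.94 | −10.7 |
| 20% | 80% | 100% | −20 | 1.25 | −16.0 |
| 30% | 70% | 100% | −30 | 1.43 | −21.0 |

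**Sensitivity to the ceiling.** Entry status need not persist over 24 months. With controls at 95% at follow-up, the differences are −5, −15 and −25 points. With controls at 90%, they are 0, −10 and −20 points.

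**All three classes required jointly.** Controls: 30%. DMP 1: 0.30 × 0.9 = 27%, 0.30 × 0.8 = 24%, 0.30 × 0.7 = 21%. The differences are −3, −6 and −9 points. SE of the difference = √(0.21 × 1.95/2000 + 0.21 × 1.95/4000) = 0.0175, or 1.75 points. The artefact is therefore about 1.7, 3.4 and 5.1 SE.

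**Change from baseline.** Controls start at 100% and can only fall. With DMP 1 unchanged, a fall in controls to 97, 95 or 90% (assumed) gives a spurious difference of +3, +5 or +10 points in favour of DMP 1.

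**Matching on drug use.** Every control is drug-treated, so an untreated DMP 1 patient has no counterpart and drops out of the matched set. The artificial difference goes to 0, but the component is then near 100% in both groups at selection and carries little information.

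**The case against.** A reader might infer that the whole comparison is biased against the DMP by construction. The documents do not support that, for four reasons.

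- **Components.** Only one of the three drug classes is an entry criterion. If the classes are analysed separately, antihypertensive and lipid-lowering prescriptions are not fixed by the selection rule.
- **Matching.** Controls are to be matched, and an article may leave the variables to the full protocol. Matching on drug use would remove the bias; matching on age could likewise remove the age difference.
- **Direction.** The Discussion names a before-after design, and on change from baseline the bias can favour DMP 1. The same section says DMP baseline values were not documented, so the article does not settle whether level or change will be compared.
- **Size.** The untreated share, the 30% joint rate, the independence of the classes and the design effect for controls are all assumptions. At the low end of the joint outcome the artefact is only about 1.7 SE.

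All four stand, and they limit the claim about direction and size. They do not restore the antidiabetic component. Without matching on drug use it is distorted, in a direction that depends on the analysis; with such matching it is near its ceiling and uninformative. The Discussion acknowledges non-random allocation, but no section addresses the overlap between entry rule and outcome.

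**Conclusion.** The point holds in this form: controls are selected on one of the three components of the primary outcome for DMP 1 versus control and DMP 1 patients are not. That component, and any joint outcome of all three classes, cannot be interpreted as written.

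In a follow-up comparison the artefact runs against DMP 1. It is about −10 to −30 points on the antidiabetic component if 10 to 30% of DMP 1 patients are untreated and controls stay near 100%, and less if controls lose their prescriptions over time. On the joint outcome it is about −3 to −9 points, with an SE of about 1.75, under the assumptions listed. In a change analysis the sign could reverse. The documents give no untreated share, so these are ranges and not estimates. The overlap itself needs no assumption; it follows from the two entry rules and Table 1. The randomised DMP 1 versus DMP 2 comparison is not affected.

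**What to change.** For the DMP 1 versus control comparison only:

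1. Apply the control group's two criteria, age over 50 and a diabetes tracer drug, to DMP 1 as well, and match within that set. Use AOK prescription data if they are available for DMP patients; otherwise use the medication recorded on the DMP documentation forms.
2. Make antihypertensive and lipid-lowering prescriptions the primary outcome, and report antidiabetic prescriptions descriptively.

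The first step removes the difference in entry rules. The second is still needed, because after the first the antidiabetic component sits near 100% in both groups at selection.

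The cost is a change to the protocol wording and to the primary outcome of this comparison, plus a data extraction whose effort depends on which source is available. The conclusion is limited to drug-treated patients over 50, and fewer DMP 1 patients are used. If the forms have to serve for DMP 1, drug treatment is ascertained from a different source than in controls, and that should be stated. The randomised comparison keeps all its patients and its own outcomes.
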